### Trial oversight structure

To ensure the trial’s scientific rigor, data integrity, and participant safety, the following committees and teams are established, with their composition, roles, and responsibilities detailed below:

#### 1. Steering committee.

Composition: The committee comprises the Principal Investigator (PI), co-principal investigators, senior interventional cardiology experts, and a methodology expert.

Roles & Responsibilities: It is responsible for the overall scientific direction, protocol implementation, and compliance of the trial. It reviews and approves protocol amendments, oversees the operation of subcommittees, and makes decisions on major issues arising during the trial conduct.

#### 2. Independent Data and Safety Monitoring Board (DSMB).

Composition: The DSMB consists of two interventional cardiology experts, one independent statistician, and one medical ethicist, all without any conflicts of interest related to this study. The DSMB is completely independent of the trial funders and the study execution team.

Roles & Responsibilities: In accordance with its independent charter, the DSMB periodically reviews unblinded cumulative safety data (particularly serious adverse events and bleeding events) after every 200 enrolled participants. It assesses the trial’s risk-benefit ratio and provides mandatory recommendations to the Steering Committee regarding trial continuation, modification, or termination.

#### 3. Endpoint adjudication committee.

Composition: This committee includes two vascular ultrasound specialists and one interventional cardiologist, all of whom are blinded to treatment group allocation.

Roles & Responsibilities: It independently adjudicates all primary endpoint events (24-hour radial artery occlusion) and predefined serious vascular complication endpoints (e.g., pseudoaneurysm, arteriovenous fistula). All imaging and clinical data for suspected endpoint events undergo centralized, blinded assessment by this committee based on pre-specified standardized definitions. Its adjudication is final.

#### 4. Data management team.

Composition: The team consists of the study coordinator, designated research nurses, and a statistician responsible for database management.

Roles & Responsibilities: It is responsible for the design of Case Report Forms (CRFs), data entry, coding, and validation (including double data entry verification and logic checks). The team implements and maintains data security and confidentiality measures. It handles missing data according to the pre-defined statistical plan (see the “Statistical methods” section) and prepares the final dataset for statistical analysis.

#### 5. Statistical team.

Composition: The team is led by one independent statistician who is blinded to treatment group allocation.

Roles & Responsibilities: The Statistical Team generates the randomization sequence, performs the final statistical analyzes while maintaining the blinding, and provides necessary safety data analyzes to support the DSMB. It reports to the Steering Committee.

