### Randomization, blinding implementation, and bias control

#### Randomization and allocation concealment.

The randomization sequence was generated by an independent statistician using dedicated statistical software. A blocked randomization method was adopted with randomly varying block sizes of 4 and 6, and the block size allocation was concealed from all investigators throughout the trial. Allocation concealment will be maintained via sequentially numbered, opaque sealed envelopes, which will only be opened after patient enrollment and prior to intervention assignment, thus preventing selection bias. The allocation sequence is concealed from investigators involved in enrollment and intervention assignment.

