#### Blinding implementation.

Given the distinct nature of the two interventions, blinding of the operators performing hemostasis or the patients is not feasible. Therefore, to minimize assessment and measurement bias, the following blinding measures are implemented: 1) blinding of endpoint assessors, with the primary endpoint (24-hour forearm RAO) assessed by an independent, group-blinded investigator using Doppler ultrasound; and 2) blinding of data analysis, with statistical analysis conducted by an independent statistician blinded to group allocation.

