#### Unblinding procedure.

Given that the treating physicians are unblinded, emergency unblinding for clinical management is not required. However, the blinding for the endpoint assessors and statisticians will be maintained throughout the trial. In the exceptional circumstance that unblinding of a participant’s allocation is deemed necessary for the safety assessment by the DSMB or for regulatory reasons, a formal request must be submitted to and approved by the Steering Committee. The unblinding will then be performed by the independent statistician who holds the allocation list, and the date and reason will be fully documented.

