### Operator training and quality control (integrated for bias mitigation)

Given the unblinded nature of operators, rigorous training and quality control will be implemented to reduce performance and detection bias, as these measures are critical for minimizing bias from non-blinded personnel:

Operator qualifications: all staff directly performing balloon pressure monitoring or assessing hemostatic efficacy will be selected from the study team and possess the required clinical credentials and routine work experience, including interventional procedures and post-procedural care.Standardized training: before trial initiation, all relevant personnel must complete a half-day centralized training. This training will cover detailed interpretation of the study protocol and procedures; principles of the system, device calibration, and demonstration of standardized operational workflows; identification and management protocols for endpoint events (e.g., forearm RAO, bleeding, hematoma); and standardized completion of case report forms (CRFs) and data management requirements.Qualification assessment: after training, each operator must successfully complete the full operational workflow for at least three simulated or real patients under the supervision of the PI or a designated supervisor. Formal qualification is granted only after confirming that the operator can execute the protocol accurately and consistently.Ongoing quality monitoring, which will be implemented as follows:(a) Periodic review: the PI will regularly audit procedural records and data to ensure protocol adherence.(b) Adverse event review: any procedure-related adverse events will trigger team discussions and retraining if necessary.(c) Blinded assessment: the primary endpoint (24-hour RAO) will be assessed by a blinded ultrasonographer to eliminate measurement bias.(d) Protocol compliance review: an independent team led by the PI will conduct periodic blinded reviews of procedural records, with group allocation concealed, to identify and address deviations.(e) Quality control for data collection of key processes: To ensure the consistency and accuracy of the high-frequency recording for key process metrics such as “active operator time,” the following measures will be implemented: (i) a designated, trained research nurse will be held solely responsible for timestamp documentation across all cases; (ii) Validated, standardized, and user-friendly timing tools (e.g., dedicated timers or tablet applications) will be used to assist in recording the timestamps of the key operational nodes. The following predefined strategy for handling missing data has already been established in the statistical plan: if the data missing rate is < 10%, a complete-case analysis will be adopted; if the missing rate is ≥ 10%, multiple imputation will be applied in sensitivity analyzes to systematically assess the potential impact of data missingness on the primary study conclusions. (iii) Specialized training for research nurses: Nurses will receive targeted training regarding the definition of “direct hands-on tasks” (including pressure adjustment, bleeding assessment, device calibration, and data documentation related to hemostasis; excluding passive observation, waiting, or auxiliary tasks not directly involved in hemostasis). Training will include the case simulations of complex scenarios (e.g., simultaneous multi-operator activities) to ensure consistent identification of task start/end times.

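### The roles given to the Statistical Team contradict the claimed blinded analysis, which cannot be relied on as described; the exposure lies mainly in the discretionary analyses

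*Protocol article*

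**What the plan says.** All references are to the protocol article.

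- **Statistical team** (Trial oversight structure, item 5): "The team is led by one independent statistician who is blinded to treatment group allocation". The same item says that the team "generates the randomization sequence, performs the final statistical analyzes while maintaining the blinding, and provides necessary safety data analyzes to support the DSMB".
- **Randomization and allocation concealment:** "The randomization sequence was generated by an independent statistician using dedicated statistical software".
- **Blinding implementation:** the second of two listed measures is "statistical analysis conducted by an independent statistician blinded to group allocation". The section Statistical software repeats this for all analyses.
- **Unblinding procedure:** endpoint assessors and statisticians are to stay blinded for the whole trial. If a participant's allocation must be revealed for a DSMB safety assessment or for regulatory reasons, "a formal request must be submitted to and approved by the Steering Committee". Then: "The unblinding will then be performed by the independent statistician who holds the allocation list".
- **DSMB** (Trial oversight structure, item 2): "the DSMB periodically reviews unblinded cumulative safety data", after every 200 participants. The board is described as fully independent of the funders and of the team running the study.

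Two other statistician roles appear: the database statistician in the Data management team, and the statistician membership of the DSMB (also in Ethical approval and study oversight). Neither is given the sequence, the list or the by-arm safety tables.

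**The concern.** Operators and patients cannot be blinded here, so the article rests its bias control on two measures: blinded endpoint assessment and blinded analysis. The second works only if the analyst cannot link patients or arm codes to treatments. Generating the sequence, keeping the list, and tabulating safety by arm for a board that sees unblinded data each give that link.

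At stake is whether the final report can truthfully state that the analysis was blinded. In practice it matters most where the analyst has latitude:

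- which deviations count as major for the per-protocol set (Analysis populations);
- which variables survive the p < 0.10 screen and the stepwise selection (Modeling and adjusted analyzes);
- which subgroups and cut-points are used, since several are given only as examples (Subgroup analyzes).

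A related wording problem concerns the DSMB. Unblinding a participant at its request needs approval from the Steering Committee, which includes the principal investigator, although the board is otherwise called fully independent and has routine unblinded access.

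**Working it through.** The point is a conflict of text, so the check sets the role statements side by side.

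| Duty | Who, according to the article | Compatible with blinding? |
|---|---|---|
| Generate the sequence | Statistical Team; elsewhere an independent statistician | No |
| Hold the list and unblind on request | The independent statistician | No |
| Safety analyses for the DSMB | Statistical Team; the DSMB sees unblinded data | No, if tabulated by arm |
| Final analysis | Statistical Team; elsewhere an independent statistician, blinded | Must be blinded |
| Lead the Statistical Team | One independent statistician, blinded | Must be blinded |

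**Step 1.** The first three duties require or give knowledge of allocation. The last two are stated to exclude it.

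**Step 2.** Item 5 puts sequence generation, DSMB support and the final analysis in one team. The list-holder carries the same job title as the blinded analyst.

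**Step 3.** Unblinding procedure conflicts with itself: it keeps statisticians blinded throughout and also names a statistician who holds the list.

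**Step 4.** The article describes no firewall inside the team, no separate unblinded statistician and no coded arms that would resolve steps 2 and 3.

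**Does any planned figure depend on this?** No. With 4.3% vs 1.0%, two-sided α 0.05 and 80% power, the unpooled normal formula is

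n per arm = (1.960 + 0.842)² × (0.043 × 0.957 + 0.010 × 0.990) / 0.033² = 368 after rounding up.

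That gives 736 in total, and 736 / 0.90 = 818 after rounding up. Both stated figures reproduce, and separating the roles changes neither.

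**How sensitive is the primary test to a few events?** The planned rates give about 0.043 × 368 = 15.8 and 0.010 × 368 = 3.7 events, so 16 vs 4. Under Analysis of the primary and secondary endpoints, the test is chi-square, or Fisher's exact test when a cell count is below 5. With n = 368 per arm, the uncorrected chi-square is (a − b)² × 736 / [(a + b)(736 − a − b)].

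| Events, control vs intervention | Fisher p | Chi-square p |
|---|---|---|
| 16 vs 4 | 0.011 | not used, one cell is below 5 |
| 16 vs 6 | 0.049 | 100 × 736 / (22 × 714) = 4.69, p = 0.030 |
| 16 vs 7 | 0.088 | 81 × 736 / (23 × 713) = 3.64, p = 0.057 |
| 14 vs 4 | 0.029 | not used, one cell is below 5 |

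Reading the cell-count rule on observed counts, 16 vs 6 and 16 vs 7 fall under chi-square. From the planned 16 vs 4, two extra intervention events or two fewer control events leave the result significant by either test shown. Three extra intervention events are needed to lose it.

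**The case against.** **One person is not shown to do everything.** The team is led by a blinded statistician; other members may generate the sequence and support the DSMB. The sections on sequence generation and on analysis each speak of an unspecified independent statistician. A firewall or coded arms could sit in the full protocol, the analysis plan or the DSMB charter. This stands: a single person is an inference from a repeated job title. It does not remove the conflict, because the article assigns the roles itself and they clash as written.

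**The primary result is well protected.** It includes all randomized patients by assignment. Occlusion is read by a blinded ultrasonographer and adjudicated by a blinded committee whose decision is final. The test is named, missing-data thresholds are fixed, and the Data management team handles missing data. Secondary, exploratory and subgroup results are declared non-confirmatory. This stands and limits the consequence.

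Three stronger readings are tempting, and the article does not support them:

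- *Moving one or two patients would overturn the primary result.* From the planned event counts three are needed, and no route is shown by which the analyst could move patients in that analysis.
- *The Steering Committee can block the DSMB's safety reviews.* The approval step covers exceptional unblinding of one participant's allocation. The scheduled unblinded reviews are granted elsewhere with no such step.
- *The compliance review cannot be blinded.* The article says that "an independent team led by the PI will conduct periodic blinded reviews of procedural records, with group allocation concealed". Pressure values must be recorded in the intervention arm, which makes concealment doubtful, but the control procedure does not expressly require air volumes to be recorded, and the method of concealment is not described. Doubt is fair; impossibility is not established.

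**Conclusion.** The contradiction is in the current text. The blinded analysis claimed under Statistical team, Blinding implementation, Unblinding procedure and Statistical software is contradicted by the duties assigned to the same team and job title, and cannot be relied on as described.

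A reader might go further and conclude that no blinded analysis exists. The article does not show that: roles may be separated in practice, but nothing in it says so.

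The size is moderate. No sample size, endpoint or planned test changes. The exposure is mainly in the per-protocol, stepwise-model and subgroup analyses. This rests on the protections of the primary comparison working as stated, and on the analyst having the discretion that the article leaves open. The Steering Committee approval step is a lesser inconsistency with the DSMB's independence and routine unblinded access.

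**What to change.** 1. **Separate the roles.** Give the sequence, the allocation list and the by-arm DSMB tables to a statistician who takes no part in the final analysis or in preparing the final dataset. The statistician who generated the sequence could keep these duties, with another team member doing the final analysis. The database statistician is not a suitable list-holder, because the Data management team handles missing data and prepares the final dataset.
2. **Code the arms.** Give the final analyst arms labelled A and B. Lock per-protocol exclusions and model specifications before decoding.
3. **Correct the claim if it is too late.** The sequence already exists and recruitment began in September 2024. If the analyst generated or has seen the list, remove the blinded-analysis claim from the four sections named above.
4. **Reconcile the unblinding wording.** State how Steering Committee approval of DSMB-requested unblinding of a participant fits with the board's independence and its routine unblinded access.

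The cost is a reassignment of duties and a wording change or, under item 3, a less favourable statement about blinding.

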### Study timeline and participant recruitment

According to the initial trial registration (ChiCTR2400088258), the planned completion date for participant recruitment was December 31, 2025. However, based on the actual enrollment rate observed since the study commenced in September 2024, it is now anticipated that the target sample size of 818 participants will be reached by May 2026. This adjusted projection reflects the current pace of recruitment, and the trial registry record will be updated accordingly to reflect this change in timeline.

### Randomization, blinding implementation, and bias control

#### Randomization and allocation concealment.

The randomization sequence was generated by an independent statistician using dedicated statistical software. A blocked randomization method was adopted with randomly varying block sizes of 4 and 6, and the block size allocation was concealed from all investigators throughout the trial. Allocation concealment will be maintained via sequentially numbered, opaque sealed envelopes, which will only be opened after patient enrollment and prior to intervention assignment, thus preventing selection bias. The allocation sequence is concealed from investigators involved in enrollment and intervention assignment.

#### Blinding implementation.

Given the distinct nature of the two interventions, blinding of the operators performing hemostasis or the patients is not feasible. Therefore, to minimize assessment and measurement bias, the following blinding measures are implemented: 1) blinding of endpoint assessors, with the primary endpoint (24-hour forearm RAO) assessed by an independent, group-blinded investigator using Doppler ultrasound; and 2) blinding of data analysis, with statistical analysis conducted by an independent statistician blinded to group allocation.

#### Unblinding procedure.

Given that the treating physicians are unblinded, emergency unblinding for clinical management is not required. However, the blinding for the endpoint assessors and statisticians will be maintained throughout the trial. In the exceptional circumstance that unblinding of a participant’s allocation is deemed necessary for the safety assessment by the DSMB or for regulatory reasons, a formal request must be submitted to and approved by the Steering Committee. The unblinding will then be performed by the independent statistician who holds the allocation list, and the date and reason will be fully documented.

### Operator training and quality control (integrated for bias mitigation)

Given the unblinded nature of operators, rigorous training and quality control will be implemented to reduce performance and detection bias, as these measures are critical for minimizing bias from non-blinded personnel:

Operator qualifications: all staff directly performing balloon pressure monitoring or assessing hemostatic efficacy will be selected from the study team and possess the required clinical credentials and routine work experience, including interventional procedures and post-procedural care.Standardized training: before trial initiation, all relevant personnel must complete a half-day centralized training. This training will cover detailed interpretation of the study protocol and procedures; principles of the system, device calibration, and demonstration of standardized operational workflows; identification and management protocols for endpoint events (e.g., forearm RAO, bleeding, hematoma); and standardized completion of case report forms (CRFs) and data management requirements.Qualification assessment: after training, each operator must successfully complete the full operational workflow for at least three simulated or real patients under the supervision of the PI or a designated supervisor. Formal qualification is granted only after confirming that the operator can execute the protocol accurately and consistently.Ongoing quality monitoring, which will be implemented as follows:(a) Periodic review: the PI will regularly audit procedural records and data to ensure protocol adherence.(b) Adverse event review: any procedure-related adverse events will trigger team discussions and retraining if necessary.(c) Blinded assessment: the primary endpoint (24-hour RAO) will be assessed by a blinded ultrasonographer to eliminate measurement bias.(d) Protocol compliance review: an independent team led by the PI will conduct periodic blinded reviews of procedural records, with group allocation concealed, to identify and address deviations.(e) Quality control for data collection of key processes: To ensure the consistency and accuracy of the high-frequency recording for key process metrics such as “active operator time,” the following measures will be implemented: (i) a designated, trained research nurse will be held solely responsible for timestamp documentation across all cases; (ii) Validated, standardized, and user-friendly timing tools (e.g., dedicated timers or tablet applications) will be used to assist in recording the timestamps of the key operational nodes. The following predefined strategy for handling missing data has already been established in the statistical plan: if the data missing rate is < 10%, a complete-case analysis will be adopted; if the missing rate is ≥ 10%, multiple imputation will be applied in sensitivity analyzes to systematically assess the potential impact of data missingness on the primary study conclusions. (iii) Specialized training for research nurses: Nurses will receive targeted training regarding the definition of “direct hands-on tasks” (including pressure adjustment, bleeding assessment, device calibration, and data documentation related to hemostasis; excluding passive observation, waiting, or auxiliary tasks not directly involved in hemostasis). Training will include the case simulations of complex scenarios (e.g., simultaneous multi-operator activities) to ensure consistent identification of task start/end times.
